#### Measurements

Professionals and pregnant women will be asked to fill out brief questionnaires. Midwives and OB-GYNs will fill out six questionnaires: one at baseline, four after each step (i.e. at each 2-month interval of the stepped-wedge design), and a sixth one 2 months after the last training. Professionals in both post-natal care and youth health care will fill out two questionnaires: one before they are trained with PROMISE and one at the end of 2018 (approximately 12 months after training). Pregnant women will fill out three questionnaires, containing questions about the smoking cessation care they receive during and after pregnancy. These questionnaires could be filled out online, via telephone, or on paper. An overview of the data collection among midwives can be found in Table 1 and Fig. 4.

**Fig. 4 Fig4:**
[figure not shown]
Schematic overview of the data collection for midwives and OB-GYNs. Midwives and OB-GYNs will receive training in four steps. They will receive a follow-up questionnaire at each step

#### Primary outcome

Our primary outcome measure is change in percentage of smoking pregnant women with whom midwives (or OB-GYNs) discussed specific quit-smoking strategies. We use the self-reported data from the questionnaires filled out by the midwives and OB-GYNs for this. We will calculate this outcome measure by dividing the number of women with whom the professional discussed specific smoking cessation strategies by the total number of smoking women seen by the professional. This will result in a percentage at each time point for each individual professional. We expected that this percentage will increase over time in the total sample, as more professionals will use the PROMISE protocol and will be better able to support smoking clients.

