#### Pregnant women

Pregnant women will be recruited through the midwifery practices and hospitals. Eligible women (1) are 18 years or older, (2) have been 0–3 months pregnant, (3) are current smokers or have quit smoking within the 6 months before pregnancy, and (4) have been registered in a practice or hospital that takes part in PROMISE. We will have no exclusion criteria. Midwives and OB-GYNs will provide recruitment materials to potential participants and inform them about the study. After providing written informed consent through their midwife of OB-GYNs, participants will receive a baseline questionnaire after 8 weeks of pregnancy and follow-up questionnaires at 2 weeks after delivery (T1) and at 6 months after delivery (T2). In those questionnaires, we assess smoking status and ask about the support they received from their midwife or OB-GYNs, post-natal care nurse professional, and youth health care professional. Women will receive a gift voucher of 10 euros for each questionnaire they complete.

This study was conducted from January 2017 to December 2019. All professionals have participated from January 2017 onwards, and the first training session has begun in March 2017. Pregnant women were able to enrol until March 2018. Among care professionals, we collected data from January 2017 to December 2017 and among pregnant women from January 2017 to December 2019.

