#### Step 1: Determine smoking behaviour and underlying motivations

Midwives assess their client’s smoking status, number of cigarettes per day, and whether the client is motivated to quit within 30 days. Smoking status is registered in the online system.

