#### Carbon monoxide meters

We added the use of carbon monoxide (CO) measurements to steps 1 and 6 of the V-MIS protocol. A carbon monoxide meter measures the CO level in someone’s expired air and can be used to determine smoking status during pregnancy [37]. While CO levels continue to be elevated for at least 24 h after smoking a cigarette, CO meters are able to determine smoking status even if someone abstained from smoking a few hours prior to measurement. CO measures offer a non-invasive way to show pregnant women how much CO potentially reaches her unborn child. CO measurements are mandatory in smoking cessation care for pregnant women in some countries [38], but they are rarely used in Dutch midwifery practices. This study is the first one to explore the use of CO measurements among pregnant women in the Netherlands.

We will train midwives to use the CO measurement as a conversation starter and to avoid using the measurement outcome in a disapproving or criticising way. They will use it to stimulate smoking cessation (step 1) or staying smoke free (step 6). We will provide specific PROMISE score forms illustrating how CO and nicotine from cigarettes reach the unborn baby. Midwives could use this to communicate the health effect of smoking to women with functional health illiteracy. In line with previous research [37], midwives will be trained to use a cut-off point of 4 part per million to identify smokers among their clients.

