#### Statistical analyses

We will use a Generalised Linear Mixed Modelling analysis in SPSS 25+ or R 3.0+ to analyse sample-wide changes in our primary outcome over time. In stepped-wedge designed studies, data should be interpreted at population level [34]. This means that not individual changes, but sample-wide changes over time are used to test the effectiveness of the new protocol (similar to a repeated cross-sectional design). In our study, all care professionals fill out a questionnaire at each of the six time points. In this questionnaire, they indicate the number of smoking women they have seen in the past month and the number whom they provided detailed smoking cessation counselling.

We calculate the percentage of smoking women who received detailed counselling for each care professional at each of the six time points. As each care professional will attend one of four training sessions, all professionals switch from the usual care condition (control) to the experimental condition at one of those time points.

Using a Generalised Linear Mixed Modelling (GLMM) analysis, we will analyse whether professionals provided detailed counselling to a higher portion of their smoking clients after receiving the training than before. We will include the factors ‘cluster’ (i.e. practices) and ‘individual’ (i.e. midwife/OB-GYN) as random effects, and ‘step’ will be included as fixed (time) effect. The exact link function (e.g. nominal, binominal) for the model will be based on the outcome variable. We will conduct an intention-to-treat analysis to control for lost to follow-up. Only members of the research team will have access to the research data.

As we do not anticipate any adverse effects in any of the two intervention arms, we will not conduct any interim analyses to determine if the trial needs to be stopped.

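### PROMISE adds CO testing that may change who is counted as a smoker at crossover, so the primary denominator may move with the intervention

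*Protocol article*

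**What the plan says.** **Outcome.** Under Primary outcome, each professional's percentage at each time point is the number of women with whom specific strategies were discussed, divided "by the total number of smoking women seen by the professional". On the source: "We use the self-reported data from the questionnaires filled out by the midwives and OB-GYNs for this". Statistical analyses confirms that one respondent supplies both counts: "they indicate the number of smoking women they have seen in the past month and the number whom they provided detailed smoking cessation counselling". Randomisation states that professionals are not blinded.

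**Recognising smokers under control.** In V-MIS step 1 the midwife assesses "smoking status, number of cigarettes per day, and whether the client is motivated to quit within 30 days". That step contains no CO test, and Carbon monoxide meters says of the devices that "they are rarely used in Dutch midwifery practices".

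**Recognising smokers under PROMISE.** The same section states: "We added the use of carbon monoxide (CO) measurements to steps 1 and 6 of the V-MIS protocol". It adds that "midwives will be trained to use a cut-off point of 4 part per million to identify smokers among their clients". Training and materials arrive together at each practice's crossover (Midwives and OB-GYNs).

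**Model.** A generalised linear mixed model with step as a fixed time effect and random effects for practice and individual compares counselling after training with counselling before it.

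**The concern.** A denominator should be fixed before, or independently of, the exposure being tested. Here it is the set of women the professional regards as smokers, and the intervention includes a tool for recognising smokers. If CO testing brings in women who would not have been counted under V-MIS, the before and after percentages describe different groups. Step 6 offers a second route, because testing women who had quit may return some of them to the count.

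The change in the percentage would then mix two things: how often recognised smokers are counselled, and who is recognised. The outcome section does not define a smoking woman in a way that is the same in both conditions. That definition belongs to the primary outcome itself and is not a detail of analysis.

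**Working it through.** **1. The plan's own yardstick.** Sample size gives 35% versus 60%, two-sided alpha 0.05, power 0.80, between-cluster CV 0.3, four clusters and 18 professionals per cluster. I used the Hussey-Hughes variance for a cross-sectional stepped wedge:

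Var = I·s²·(s² + T·t²) / [(I·U − W)·s² + (U² + I·T·U − T·W − I·V)·t²]

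- I = 4 clusters, T = 6 time points, one cluster crossing at each of T1 to T4. This gives U = 14, W = 46, V = 54.
- s² = 0.475 × 0.525 / 18 = 0.01385, with 0.475 the mean of 35% and 60%.
- t² = (0.3 × 0.35)² = 0.01103.
- Var = 0.00765, so SE = 0.0875. Power = Φ(0.25/0.0875 − 1.96) = 0.815. With 17 per cluster it is 0.795.

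The stated 18 therefore reproduces. Other reasonable settings give 16 to 20. The planned 25 points are the right scale for judging a denominator shift.

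**2. Effect of a shift.** Let b be coverage among women who would be counted as smokers without CO, u the extra CO-identified women as a fraction of them, and q coverage among those extra women.

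Reported PROMISE rate = (b + u·q)/(1 + u), so bias = u·(q − b)/(1 + u).

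The bias is zero when u = 0 or q = b, negative when q < b and positive when q > b. The documents give neither u nor q. The values below are assumptions, with q run over its whole range from 0 to 1.

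| u | Reported rate if b stays 35% (q = 0 to 1) | Spurious change | Reported rate if b rises to 60% (q = 0 to 1) | Reported contrast (true: 25) |
|---|---|---|---|---|
| 0.10 | 31.8% to 40.9% | −3.2 to +5.9 points | 54.5% to 63.6% | 19.5 to 28.6 points |
| 0.20 | 29.2% to 45.8% | −5.8 to +10.8 points | 50.0% to 66.7% | 15.0 to 31.7 points |
| 0.30 | 26.9% to 50.0% | −8.1 to +15.0 points | 46.2% to 69.2% | 11.2 to 34.2 points |

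Example: u = 0.20, b = 0.60, q = 0 gives 0.60/1.20 = 0.50, and 50 − 35 = 15 points. With q = 0.60 it gives (0.60 + 0.12)/1.20 = 0.60, so no bias. At u = 0.20, power at 18 per cluster would lie between about 0.41 and 0.95 instead of 0.815.

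**3. Why the model does not separate the two.** The fixed step effect removes calendar trends common to all practices. The random effects absorb stable differences between practices and between individuals. A change in recognising smokers would start at each practice's own crossover, so it has the same time pattern as the intervention and would be estimated as part of it.

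**4. What the held data can show.** Table 1 lists the count of smoking clients in the preceding month at T0, T1 to T4 and T5. If CO adds a fraction u and nothing else changes, that count rises by the factor 1 + u at crossover. A log-link count model with the same structure estimates this ratio directly.

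**The case against.** The strongest reply is that the link is inferred. A reader might conclude that the two conditions are certainly scored on different women. The documents do not support that: no section says that a CO-only positive enters the questionnaire count, and CO is also described as a way to open the conversation. Nor can one say that CO is used only after crossover (the text says rarely), or that the counts come from recall: they cover the past month, smoking status is registered online, and how the counts are retrieved is not stated. All of this stands and limits the point to a possible shift of unknown size.

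A reader might also infer that the shift must dilute the effect. That holds only if CO-only women are counselled less than other smokers; they could be counselled equally or more.

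Nor can it be said that the trial has no means of detecting the shift. The smoker count is a listed outcome at all six time points. What is not described is a model of that count set beside the primary result.

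It could be argued that the women's own reports should settle the matter, since "we assess smoking status and ask about the support they received from their midwife or OB-GYNs". How those reports are analysed may be specified outside the article, so nothing can be concluded from its silence. They would also be a poor check. Table 1 collects midwife use of protocol elements only at the women's T1, two weeks after delivery. A woman 8 weeks pregnant in January 2017 would deliver around August or September. With training from March 2017 at two-month steps, three of the four steps would have crossed over by then and the fourth would be due, so almost no pregnancy would be wholly under control.

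Finally, restricting the denominator to disclosed smokers leaves out women whom CO testing is meant to reach. That is fair, and is why they need their own tally.

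**Conclusion.** The point holds as a threat to the interpretation of the primary outcome, not as a demonstrated bias. CO identification of smokers is part of PROMISE, the denominator is smokers as counted by an unblinded professional, no common definition is fixed for the two conditions, and the planned model would attribute any shift at crossover to PROMISE.

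The size cannot be read from the documents. Under the assumed 10% to 30% of extra recognised smokers, the spurious change with no change in counselling of already recognised smokers runs from about −8 to +15 points. These are outer limits, with none or all of the added women counselled. The upper end needs trained midwives to counsel every CO-only woman while other smokers stay at 35%, which is not a likely pattern. The figures show that the effect could matter against 25 points, not that it does. Because it can be checked with data already held, it should be checked.

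**What to change.** **Definition.** State one denominator for both conditions: women who self-report smoking before any CO reading. Tally CO-only positives separately. Registered smoking status serves this purpose only if it can be shown to precede the CO reading, because PROMISE places the test in the same step 1.

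**Closed data.** The section on pregnant women says that professional data were collected from January to December 2017, so a new questionnaire line is no longer possible. Instead:

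1. Fit the same stepped-wedge model, with a suitable count link, to the smoking clients reported at T0 to T5.
2. Report the estimated shift at crossover, with its interval, next to the primary result.
3. If there is a shift, give a sensitivity range for the primary effect, using the estimated u in the formula above and q from 0 to 1.

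The number of women counselled per month is not a substitute: it also rises when CO finds new smokers who are then counselled.

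**Cost.** One more model on existing data. The self-report denominator leaves out CO-only women, so they must be reported separately. The count check has limits too: the count could also move through quitting or caseload, so a flat result is reassuring but not proof.

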#### Statistical analyses

We will use a Generalised Linear Mixed Modelling analysis in SPSS 25+ or R 3.0+ to analyse sample-wide changes in our primary outcome over time. In stepped-wedge designed studies, data should be interpreted at population level [34]. This means that not individual changes, but sample-wide changes over time are used to test the effectiveness of the new protocol (similar to a repeated cross-sectional design). In our study, all care professionals fill out a questionnaire at each of the six time points. In this questionnaire, they indicate the number of smoking women they have seen in the past month and the number whom they provided detailed smoking cessation counselling.

We calculate the percentage of smoking women who received detailed counselling for each care professional at each of the six time points. As each care professional will attend one of four training sessions, all professionals switch from the usual care condition (control) to the experimental condition at one of those time points.

Using a Generalised Linear Mixed Modelling (GLMM) analysis, we will analyse whether professionals provided detailed counselling to a higher portion of their smoking clients after receiving the training than before. We will include the factors ‘cluster’ (i.e. practices) and ‘individual’ (i.e. midwife/OB-GYN) as random effects, and ‘step’ will be included as fixed (time) effect. The exact link function (e.g. nominal, binominal) for the model will be based on the outcome variable. We will conduct an intention-to-treat analysis to control for lost to follow-up. Only members of the research team will have access to the research data.

As we do not anticipate any adverse effects in any of the two intervention arms, we will not conduct any interim analyses to determine if the trial needs to be stopped.

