**Fig. 1 Fig1:**
[figure not shown]
Overview of clusters of midwifery practices. Midwifery practices from three regions will be randomly allocated to one of four steps. At each step, practices that received training cross over from the control condition (V-MIS/usual care) to the experimental condition (PROMISE)

We will train clusters of midwives and OB-GYNs, subsequently, at four regular intervals (‘steps’). At each step, practices that received training cross over from the control condition to the experimental condition. We will measure outcomes at baseline, at each of the four steps (2 months apart, step 1 starting 2 months after baseline) and 2 months after the last step.

This study has been registered in the Dutch Trial Registry (NTR 6305) and was exempt from medical ethics review by the Ethics Committee of the Erasmus Medical Centre in Rotterdam (MEC-2016-605).

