#### Midwives and OB-GYNs

After receiving informed consent from midwives and OB-GYNs, we will randomly assign their practices to one of four steps. We will follow a training and cross-over procedure in accordance to our stepped-wedge study design. At baseline, all clusters of practices will use the existing V-MIS protocol for supporting women to quit smoking (i.e. control group). Two months after baseline, we will train the first cluster of practices (i.e. step 1) and will provide them with the PROMISE materials. From that moment onwards, this first cluster will cross over to the experimental condition and will continue to use the new PROMISE protocol. We will train clusters 2, 3, and 4 subsequently, each at a 2-month interval. After training, these clusters also cross over to the experimental condition. This way, we will train all practices in 4 steps over a 10-month period and all practices will be using the PROMISE protocol from month 8 onwards. By gradually implementing the PROMISE protocol among clusters of practices, we will replicate a real-life implementation of protocols that require face-to-face training. The order at which practices will receive the face-to-face training will be randomised at the practice level and stratified by region. We had no inclusion or exclusion criteria for the midwives and OB-GYNs, other than being employed at one of the practices enrolled in our study. At the start of the study (January 2017), participating midwives will complete a baseline questionnaire (T0) about their level of support to smoking pregnant women. They will receive a similar questionnaire at each step of the study (T1–T4) and will receive a final questionnaire 2 months after the final step (T5). These questionnaires include our main outcome variables. Figure 1 provides a schematic overview of the training steps. Care professionals will receive no incentive for filling out the questionnaires, but those who complete the training will receive continuing education credits.

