### Outcomes

Table 1 represents an overview of all outcomes collected among professionals and pregnant women/mothers. All outcomes for pregnant women measure their current status. Health status, for example, is measured by asking ‘How healthy do you feel?’ with response options (1) ‘Healthy’, (2) ‘Sometimes healthy, sometimes unhealthy’, and (3) ‘Unhealthy’.

**Table 1 Tab1:** Outcome measures

	Measurements^a^		
**Midwives and OB-GYNs**	T0	T1–T4	T5
Background characteristics	x		
Number of smoking clients seen in past month	x	x	x
% smoking cessation discussed	x	x	x
% specific/individual strategies for smoking cessation discussed	x	x	x
Use of protocol components	x	x	x
Barriers and facilitators of using protocol elements	x	x	x
Transferral of smoking status to post-natal care	x	x	x
Appreciation of PROMISE			x
**Post-natal care and youth health care**	T0	T1	
Background characteristics	x		
Use of protocol components^b^	x	x	
Transfer of smoking status from midwife	x	x	
Transfer of smoking status between post-natal care and youth health care	x	x	
Appreciation of PROMISE		x	
**Pregnant women/mothers**	T0	T1	T2
Background characteristics	x		
Smoking status	x	x	x
Partner’s smoking status	x	x	x
Exposure to environmental smoke	x	x	x
Perceived health status	x	x	x
Self-efficacy	x	x	x
Perceived health effects of smoking	x	x	x
Baby background characteristics		x	
Appreciation of protocol elements		x	x
Use of protocol elements by midwife		x	
Use of protocol elements by post-natal care		x	
Use of protocol elements by youth health care			x

^a^Midwives and OB-GYNs: follow-up at each step (every 2 months); post-natal care nurses and youth health care: before training (T0) and 1 year after training (T1); pregnant women/mothers: after 8 weeks of pregnancy (T0), 2 weeks after delivery (T1), and 6 months after delivery

^b^Motivational interviewing techniques only

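### T1–T4 coincide with training but recall the past month, so on the stated crossover rule each practice's own-step report counts mainly pre-training care as PROMISE

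*Protocol article*

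**What the plan says.** All references are to the protocol article.

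- **Recall window.** Under Statistical analyses, professionals complete six questionnaires in which "they indicate the number of smoking women they have seen in the past month" and how many of these women received detailed counselling. Table 1 lists "Number of smoking clients seen in past month" at T0, T1–T4 and T5.
- **Measurement times.** Study design sets measurements at baseline, "at each of the four steps (2 months apart, step 1 starting 2 months after baseline) and 2 months after the last step", that is, months 0, 2, 4, 6, 8 and 10. The section on midwives and OB-GYNs agrees: "They will receive a similar questionnaire at each step of the study (T1–T4"). So does the caption of Fig. 4.
- **Training times.** "Two months after baseline, we will train the first cluster of practices (i.e. step 1"), with the other three groups following at 2-month intervals. The same section has a practice cross over from the moment of training and all practices on PROMISE from month 8.
- **Change of condition in the analysis.** Statistical analyses states that "all professionals switch from the usual care condition (control) to the experimental condition at one of those time points". The model has random practice and individual effects and step as a fixed time effect. The condition indicator is not written out.
- **A different wording on timing.** Measurements describes "four after each step (i.e. at each 2-month interval of the stepped-wedge design"), with the sixth questionnaire 2 months after the last training.

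**The concern.** A practice trained at month 2 that answers T1 at month 2 reports on month 1 to month 2, when it was still using V-MIS. The only crossover rule in the article makes T1 its first PROMISE observation. The same happens to the later groups at T2, T3 and T4. No lag, transition period or exclusion of the own-step report is stated.

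Only a few cells are affected, but they matter. Once period is adjusted for, much of the information on the treatment effect comes from comparing groups that have just crossed over with groups that have not. If those cells carry the wrong label, a programme that works could be reported as having little or no effect on the primary outcome.

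**Working it through.** **Inputs.** From Sample size: 35% versus 60% (25 points), two-sided α = 0.05, between-cluster CV 0.3, 18 professionals per cluster, a four-cluster design. From Study design: six time points, crossover at the second to fifth. Assumed: immediate and constant effect, linear approximation to the GLMM, equal cluster sizes.

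**1. Reproducing the plan's figure.** I used the Hussey–Hughes variance with I = 4 clusters (one per step) and T = 6. The cluster-period variance is σ² = 0.475 × 0.525 / 18 = 0.01385. The between-cluster SD τ is 0.3 × 0.35 = 0.105 or 0.3 × 0.475 = 0.1425, because the article does not say which proportion the CV refers to.

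If a group is coded PROMISE from its own step onwards, the row totals are 5, 4, 3, 2 and the column totals 0, 1, 2, 3, 4, 4. So U = 14, W = 46 and V = 54, and

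Var = Iσ²(σ² + Tτ²) / [(IU − W)σ² + (U² + ITU − TW − IV)τ²] = 4σ²(σ² + 6τ²) / (10σ² + 40τ²).

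- τ = 0.105: SE = 0.0875, power = Φ(0.25/0.0875 − 1.96) = 0.815.
- τ = 0.1425: SE = 0.0889, power = 0.803.

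Eighteen is the smallest cluster size that reaches 0.80, so the stated figure is reproduced.

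**2. Miscoded cells.** Coded PROMISE: 5 + 4 + 3 + 2 = 14 of 24. If no part of the own-step recall month follows training, truly PROMISE: 4 + 3 + 2 + 1 = 10. Four cells differ.

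**3. Share of the effect kept when none of the window follows training.** Regressing the true exposure (one period later) on the coded exposure, with the same weights and fixed period effects, gives

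e = (4σ² + 4τ²) / (10σ² + 40τ²).

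| Setting | Share kept | 25 points becomes |
|---|---|---|
| τ = 0 (no between-cluster variance) | 0.40 | 10.0 |
| τ = 0.105 | 0.0995/0.5795 = 0.172 | 4.3 |
| τ = 0.1425 | 0.1366/0.9508 = 0.144 | 3.6 |
| limit of τ large relative to σ (equivalent to fixed practice effects) | 0.10 | 2.5 |

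Splitting the 26 practices and departments 7/7/6/6 gives practically the same range. At the protocol's inputs, power is Φ(0.25 × 0.172/0.0875 − 1.96) = 0.07 and Φ(0.25 × 0.144/0.0889 − 1.96) = 0.06.

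**4. Partial overlap.** If a fraction f of the recall month follows training, the share kept is e + (1 − e)f.

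- f = 0.5: 0.10 + 0.90 × 0.5 = 0.55 up to 0.40 + 0.60 × 0.5 = 0.70.
- f = 1: 1.00.
- More than half is lost only while f is below (0.5 − e)/(1 − e): 0.17–0.44 over the whole range, about 0.40–0.42 at the protocol's inputs.

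**5. Possible codings of the own-step report.**

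- *Always control.* With f = 0 the slope is 1.00. The design sums become U = 10, W = 30, V = 30, which give the same 10σ² + 40τ², so SE and power are unchanged. With f > 0 the share kept is 1 − (1 − e)f: 0.55–0.70 at f = 0.5 and 0.33–0.55 at f = 0.75. This is the mirror-image bias.
- *Fractional.* The slope is 1.00 at any f. At f = 0.5 the SE rises by 1/√((1 + e)/2), to 0.114–0.118, so power is about 0.57–0.59.
- *Excluded.* The slope is 1.00, the SE 0.120–0.123 and power 0.53–0.55.

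**The case against.** The strongest objection is that the miscoding is inferred. The article never writes out the condition indicator. Its model paragraph describes the comparison as counselling after training against counselling before it, and on that wording a report on a wholly pre-training month could be treated as *before*. Row-level coding may also be set out in an analysis plan that is not shown. This stands as a limit on certainty. It does not remove the point, because the article itself fixes the measurement times, the recall window and the moment of crossover, and followed literally these rules conflict.

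The second objection is that *after each step* may mean a real delay. A full 2-month delay would make T4 coincide with T5, but a delay of about one month would not, and it would put the whole window after training. Professional data collection ran from January to December 2017, slightly longer than a strict 10-month grid, and no completion deadline is given. Against this, Measurements equates the phrase with the 2-month marks, and Study design spaces all measurements evenly, with the last one 2 months after the last step. Timing at the step is the better-supported reading, but it is not established.

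A reader might therefore infer that the plan certainly discards about 90% of the effect. The documents do not support that. The figure needs a window with no post-training days and, in effect, fixed practice effects, whereas the article plans random ones. Late returns would reduce the loss.

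**Conclusion.** The concern holds in conditional form. As written, training and T1–T4 share the same dates, the outcome looks back one month, and the only stated crossover rule counts the own-step report as PROMISE. The resulting bias is towards no effect. Its size depends on how much of the recall month follows training: 10–40% of the effect is kept if none does, 55–70% if half does, and all of it if the whole month does. At CV 0.3 and 18 per cluster the worst case turns 25 points into about 4.

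These figures rest on an immediate, constant effect, fixed period effects, a linear approximation and the inferred coding. Without a time effect 0.67–0.71 would be kept in the worst case, but the plan includes one. The power figures belong to the four-cluster calculation that reproduces 18, not to the planned model with practices as clusters. The conflict should be settled before the primary model is fitted.

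**What to change.** Define exposure by the recall window, from the practice's randomised training date and the questionnaire's completion date:

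- control if the window ends by the training date;
- PROMISE if the window starts on or after it;
- otherwise the fraction of the window after training.

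Do not force straddling reports to control, since that brings in the mirror-image bias. As a sensitivity analysis, exclude own-step reports; this is unbiased under the same assumptions but less precise. Make Study design, the section on midwives and OB-GYNs, Measurements and the caption of Fig. 4 agree on whether questionnaires come at the step or after it, and by how much.

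The cost is some extra data handling and no new outcome data, assuming that training and completion dates were recorded. No power is lost when own-step windows lie wholly before training. Where they straddle it, precision falls, as shown for f = 0.5, because those reports carry less contrast. The fractional coding also assumes that clients are spread evenly over the month.
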